## H. Permanent Income

- Permanent income is defined as the average of household income in the last calendar year and at age 35 divided by the number of adults living in the household:

$$\frac{\text{Average of household income in the last calendar year and at age 35 (scaled for inflation)}}{\text{Number of adults in the household}}$$

- We use the average of household income in the last calendar year and at age 35 (scaled for inflation) if both are available and non-zero. If either measure is missing or zero, we use only the available, non-zero income
  - Household income in last calendar year is the sum of household income from the following sources:
    - *In the last calendar year, what was your pre-tax household income from the following sources? Income from wages or salaries, Income from self-employment, Income from public and private pensions, Income from Social Security, Income from unemployment benefits, Income from any other social benefits, assistance, or grants (e.g., veteran's benefits, disability benefits), Income from investments, savings, insurance, or property (including dividends, interest, and rent from rental property), Income from any other sources*
- Stated total household income at 35 is scaled for inflation to the last calendar year using the CPI when the respondent was 35 and the CPI in the year prior to when the respondent completed the survey
  - *What was the total pre-tax annual income of your household when you were 35 years old? (If you don't know the exact figure, please give your best estimate.)*
- Number of adults currently living in the household
  - *Including yourself, how many people in each of the following age groups is currently living in your household? Adults*
  - Note: if this question was left blank, we assume two adults if married and one adult if never married or divorced

## I. Net worth / permanent income

- Net worth divided by permanent income

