#### **A. Primary outcome variables**

- Net worth n=109
- Permanent income n=112
- Net worth / permanent income n=109
- Annual amount of interest above 6% on high cost debt n=109
- Percent of later choices in money sooner vs. later tradeoffs n=112
- Measure of misuse of credit cards n=113
- Savings rate with permanent income as a control on the RHS n=106
- General measure of financial situation n=113
- Educational attainment in years n=113
- Index of forward-looking behaviors n=113
- Social status n=113

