## G. Net Worth

- Net worth = sum of assets – sum of debt
- Assets
  - *What is the current balance or total value of financial assets held by your household in the following types of accounts: Checking accounts, Savings accounts, Money market accounts, Certificates of deposit (CDs), Tax-deferred retirement accounts (e.g., IRAs, 401(k) accounts, Keogh accounts), Other tax-deferred savings accounts (e.g., education savings accounts, health savings accounts), Bonds not included in tax-deferred accounts, Stocks not included in tax-deferred accounts, Other assets not listed above*
  - *Please indicate the total market value for each of the following types of assets. That is, what would they be worth if they were sold today? If you are not sure of the exact figures, please provide a rough estimate. Your primary residence, Additional residence(s) or vacation home(s), not including rental properties, Rental properties, Other real estate, Business(es) or farm(s), Vehicles (any cars, trucks, boats, trailers, motor homes, airplanes or other vehicles), Other assets such as trusts, commodities, valuable art, jewelry, coins, collectibles, or other items*
- Debt
  - *Please indicate the amount you currently owe for any of the following items. If you are not sure of the exact figures, please provide a rough estimate. Home mortgage for your primary residence, Second mortgage, home equity loans or lines of credit, or home improvement loans for your primary residence, Mortgage(s), home equity loans or lines of credit, or other loans for your secondary residence(s), Mortgage(s), home equity loans, lines of credit, or other loans for your rental property, Other real estate loans, Business or farm loans, Vehicle loans, Credit cards or other revolving accounts (only if you carry forward a balance; do not include balances that are paid off each month), Installment loans for major purchases (e.g., appliances or furniture), Educational loans, Other personal loans, Medical bills*

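### The primary outcome net worth / permanent income puts net worth not divided by adults over per-adult income, so it partly reflects how many adults live in the home

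*SAP*

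**What the plan says.** Section III.A lists the ratio among the 11 primary outcomes: "Net worth / permanent income n=109". Its whole definition, in section VIII.I, is "Net worth divided by permanent income".

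The two parts are defined separately:

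- **Denominator (VIII.H).** Permanent income averages household income in the last calendar year and at age 35, the latter adjusted for inflation, "divided by the number of adults living in the household". The divisor is the number of adults in the home at the time of the survey. If that answer is blank, two adults are assumed for married respondents and one for those never married or divorced.
- **Numerator (VIII.G).** "Net worth = sum of assets – sum of debt". Nothing is divided by the number of adults. The account question asks for the "total value of financial assets held by your household". The question on real estate, businesses, vehicles and other assets names no unit and opens "Please indicate the total market value for each of the following types of assets"; its list includes the primary residence. The debt question is addressed to the respondent, "Please indicate the amount you currently owe for any of the following items", and its list includes the mortgage on that residence.

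Section II then replaces every variable except gender by the inverse normal of its percentile rank. The primary model in section III has the key predictor and a male indicator, with permanent income added only for savings rate. It has no term for household size.

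**The concern.** A wealth-to-income ratio can be read only if both parts refer to the same unit. Here the denominator is per adult and the numerator is not. Two respondents whose households hold the same wealth relative to income receive different scores if one lives alone and the other with a partner or a grown child.

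The outcome is tested against both primary predictors. It therefore enters both false-discovery-rate families and both joint Wald tests (section VI.A). If the number of adults is unrelated to the predictor, the mismatch adds noise to an analysis of 109 people. If it is related, part of the fitted coefficient describes household composition rather than wealth relative to income. None of the robustness checks in section V changes the definition of this ratio.

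**Working it through.** **1. Algebra from the SAP's definitions.** Let NW be net worth, Y the average household income of VIII.H before division, and A the number of adults.

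- Permanent income = Y / A
- Ratio in VIII.I = NW / (Y / A) = A × (NW / Y)

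The SAP gives no figure for this ratio to reproduce. With illustrative values NW = $600,000 and Y = $150,000:

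| Adults | SAP ratio | NW / Y | (NW / A) / (Y / A) |
|---|---|---|---|
| 1 | 4.0 | 4.0 | 4.0 |
| 2 | 8.0 | 4.0 | 4.0 |
| 3 | 12.0 | 4.0 | 4.0 |

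The two matched definitions agree for every A. The SAP's definition agrees with them only when A = 1.

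**2. Does the transformation remove the factor?** Ranks are unchanged when every value is multiplied by the same positive constant. A is recorded for each respondent, so it is not a common constant and the ordering changes. With positive net worth, more adults move a respondent up. With negative net worth, which assets minus debt allows, more adults move the respondent down.

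**3. Illustrative size.** The SAP reports no distribution of A, so everything in this step is assumed:

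- 25%, 60% and 15% of homes have 1, 2 and 3 adults.
- NW / Y is positive and log-normal, with log-SD s of 0.8 to 1.3.
- A is unrelated to NW / Y.
- The predictor has no true effect and has correlation r with log A.

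On the log scale, log(ratio) = log(NW / Y) + log A.

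- Mean of log A = 0.60 × 0.693 + 0.15 × 1.099 = 0.581
- Variance of log A = 0.60 × 0.693² + 0.15 × 1.099² − 0.581² = 0.132
- Share of outcome variance due to log A = 0.132 / (0.132 + s²)
- Spurious correlation = r × √share

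| s | Share | r = 0.2 | r = 0.05 |
|---|---|---|---|
| 0.8 | 0.17 | 0.083 | 0.021 |
| 1.0 | 0.12 | 0.068 | 0.017 |
| 1.3 | 0.07 | 0.054 | 0.013 |

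**4. Check on the analysed scale.** A simulation that applied the rank and inverse-normal step gave nearly the same correlations. Under the same assumptions, two-adult homes sat about 0.5 to 0.8 SD above one-adult homes although their true ratios had the same distribution. When 8% of net worths were made negative (a further assumption), the r = 0.2 figures fell to about 0.04 to 0.06.

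**The case against.** Five points can be made for the plan as it stands.

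- **The numerator may not be wholly household-level.** Only the account question names the household. This stands as a limit on the wording: for property and debts, household level is the natural reading, because whole market values and the whole mortgage are requested, but it is inferred. It does not rescue the definition, since no part of VIII.G puts net worth on a per-adult basis.
- **A factor of 2 or 3 describes the raw ratio, not the variable analysed.** This is correct. The factor is 1 in one-adult homes, and only differences in A between homes matter after ranking. The illustration therefore also has to be judged on the transformed scale.
- **The magnitude is driven by assumptions.** This stands too. The spurious correlation is proportional to the assumed r. At r = 0.2 it matches or exceeds the prior mean of 0.05 that section VI.C gives for delay ability, but 0.2 is itself four times that prior mean. At r = 0.05 it is about 0.02 or less. Even 0.083 is below one standard error of a correlation at n = 109, roughly 1/√106 = 0.097.
- **It is one outcome of 11.** Net worth and permanent income are also tested separately, and this point leaves those analyses unaffected.
- **The mixed basis might be deliberate.** The SAP gives no reason for it. Section IX records only that outliers in the ratio were traced to one component or the other.

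A reader might infer that any link between self-control and living with a partner must appear as a link with wealth relative to income. The documents do not support that. It presumes that the number of adults is unrelated to the household ratio itself. Such a relation could offset the artefact or add to it, and negative net worth reverses its direction.

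**Conclusion.** The definition in VIII.I is inconsistent with those in VIII.G and VIII.H. That much follows from the SAP's text, with household level inferred for property and debts, and it needs no assumption about the data. The outcome partly reflects household composition, and neither the transformation nor the covariates take this out.

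The effect on this sample cannot be computed, because the SAP gives neither the distribution of adults per home nor their relation to the predictors. The ranges of about 0.05 to 0.08 (r = 0.2) and 0.013 to 0.021 (r = 0.05) are illustrations. They require positive net worth, the assumed household mix and spread, and no relation between adults and the true ratio. Nothing in the SAP shows that a conclusion would change, so a claim that the primary results are invalid would go too far. The point ranks as one that should be fixed: a real defect in one primary outcome, of unknown and possibly small effect, with a nearly free remedy.

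**What to change.** In VIII.I, define both parts on one basis. Use either net worth divided by average household income before the division by adults, or net worth per adult divided by permanent income. The two are algebraically identical, so there is no modelling choice to settle. Leave VIII.H as it is for the permanent-income outcome, and state in VIII.G that net worth is measured at household level.

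If the mixed basis is intended, VIII.I should say why, and the matched ratio should be added to section V as a sensitivity analysis.

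The cost is one line of SAP text for the ratio, a clarifying sentence in VIII.G and one line of code. No new data are needed. The sample should stay at 109, since the number of adults already enters the denominator.

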## J. Annual amount of interest above 6% on high cost debt

- Respondents selected an interest rate bucket for each type of debt. We assumed the interest rate is the midpoint of the selected category (i.e., if selected 5-8% bucket, the interest rate is assumed to be 6.5%)
- “High Cost Debt” is any debt for which the interest rate is greater than 6%
  - We chose the 6% interest rate threshold as an interest rate above which there is, for the most part, no good excuse to be paying that high an interest rate. We assume subjects with debt at an interest rate above 6% are either:
    1. Financially incompetent (e.g., have not refinanced their mortgage rates despite low interest rates in the last few years)
    2. In financial distress (e.g., have high leverage ratio on their collateralized debts or have bad credit)
- For each high cost debt category we calculate the amount of interest above 6% as the dollar amount of debt multiplied by the interest rate above 6%

$$\sum_{\text{All high cost debt categories}} (\text{interest rate} - 6\%) \times \text{total amount owed}$$

- Please indicate the amount you currently owe for any of the following items. If you are not sure of the exact figures, please provide a rough estimate. Home mortgage for your primary residence, Second mortgage, home equity loans or lines of credit, or home improvement loans for your primary residence, Mortgage(s), home equity loans or lines of credit, or other loans for your secondary residence(s), Mortgage(s), home equity loans, lines of credit, or other loans for your rental property, Other real estate loans, Business or farm loans, Vehicle loans, Credit cards or other revolving accounts (only if you carry forward a balance; do not include balances that are paid off each month), Installment loans for major purchases (e.g., appliances or furniture), Educational loans, Other personal loans, Medical bills
- Please indicate the interest rate for each of those items. If you are not sure of the exact figures, please provide your best estimate.

| 0-4%                  | 5-8%                  | 9-12%                 | 13-16%                | 17-20%                | 21-24%                | >24%                  |
|-----------------------|-----------------------|-----------------------|-----------------------|-----------------------|-----------------------|-----------------------|
|  |  |  |  |  |  |  |

## K. Percent of later choices in money sooner vs. later tradeoffs

- Percent of questions for which the respondent selected the “money later” instead of the “money sooner” option in the tradeoff questions
  - Which would you prefer? (A) getting \$X today (B) getting \$Y thirty days from today
  - Which would you prefer? (A) getting \$X thirty days from today (B) getting \$Y sixty days from today

#### L. Measure of misuse of credit cards

- The measure of misuse of credit cards is calculated as the average of the transformed responses (percentile inverse normal) to the following four questions about the subject's credit card usage. Percentile ranks for the sample are calculated after recoding the variables such that a higher score corresponds to higher misuse of credit cards.
  1. **Amount of carried credit card debt:** *Please indicate the amount you currently owe for any of the following items: Credit cards or other revolving accounts (only if you carry forward a balance; do not include balances that are paid off each month)*
  2. **Annual amount of interest above 6% on high cost credit card debt:** *Please indicate the amount you currently owe for any of the following items: Credit cards or other revolving accounts (only if you carry forward a balance; do not include balances that are paid off each month). Please indicate the interest rate for each of those items. If you are not sure of the exact figures, please provide your best estimate*
  3. **Binary measure of having been denied credit for a credit card in the last year:** *Have you been denied credit for any type of credit card within the last calendar year?*
  4. **Number of late payments in the last year:** *How many times have you made a late payment on any credit card bills in the last calendar year?*
- Note: For respondents who did not fill in a value for carried credit card debt, we assume \$0 credit card debt if they reported non-zero debt in other debt categories in the same question and either report owing \$0 on their credit cards each month or report paying off 100% of their credit card bill each month

#### M. Savings Rate

- Savings rate over the last few years as a percentage of income
- We will run regressions on savings rate with and without permanent income as a control:
  - Without controlling for permanent income, we will measure the effect of delay of gratification on savings rate (possibly through income)
  - Controlling for permanent income, we will measure whether delay of gratification impacts savings rate above and beyond the relationship through income
- Note: Reported savings rates of 70% and higher are suspect and excluded from analyses (n=4). These four respondents are believed to be out of the work force or second-earners in their household
- *On average each year, over the past few (e.g., 3-5) years, what percent of your income have you saved? Please include all forms of saving, including retirement accounts and other savings accounts.*

#### **N. General measure of financial situation**

- The general measure of financial situation is calculated as the average of the transformed responses (percentile inverse normal) to the following three questions about the subject's financial situation. Percentile ranks for the sample are calculated after recoding the variables such that a higher score corresponds to a better financial situation
  1. *In general, would you say you (and your family living with you) have more money than you need, just enough for your needs, or not enough to meet your needs? (more money = better financial situation)*
  2. *How difficult is it for you (and your family living with you) to pay your monthly bills? Very difficult – Not at all difficult (less difficult = better financial situation)*
  3. *Using a scale from 0 to 10 where 0 means “the worst possible financial situation” and 10 means “the best possible financial situation,” how would you rate your financial situation these days? (higher rating = better financial situation)*

#### **O. Educational attainment (years of education post-high school)**

- We calculate the number of years of post-high school education based on reported degrees received. This is calculated as the sum of the base years of education and any additional years
- “Base years of education” is determined by the highest of the following degrees
  - Associate's Degree: 2 years post-high school
  - Bachelor's Degree: 4 years post-high school
  - Master's Degree: 6 years post-high school
  - PhD: 9 years post high-school
- “Additional years” are added for each of the following degrees
  - Law Degree: + 3 years
  - Medical Degree: + 4 years if highest degree is BA or MA, + 3 years if PhD
  - Second Master's degree: + 2 years
  - Teaching Credential: + 1 year
  - One year post-Master's program: + 1 year
- *For any degree(s) that you hold, please specify below the type of degree you have earned and specify the college, university, or institution that granted it*
- *What is the highest level of education you have attained? High school diploma or equivalent, Some college education, College degree, Some graduate or professional education, Graduate or professional degree*

#### **P. Education Scale from Ayduk et al (2000)**

- Highest educational level: high school = 1, correspondence courses = 2, college = 3, master's = 4, and PhD = 5
- We will try to find out exactly how categorization was done in the earlier paper (e.g., how law degrees were treated), but without any more information, we will classify medical degrees with doctorates, law degrees as between a Master's and PhD/Medical Degree (4.5), and 2-year degrees with correspondence courses

## Q. Quantitative and verbal SAT scores

- Parent-reported quantitative and verbal SAT scores from the 1984 follow-up (subjects were about 18 years old)

## R. Index of forward-looking behaviors

- Z-scores are calculated by taking inverse normal of the percentile ranks for each question after recoding the variables such that a higher score corresponds to better self-regulation. To create the composite measure, Z-scores are aggregated first by sub-section (e.g., diet, exercise), then by category (e.g., diet+ exercise + BMI), and finally across all five categories. Scores are renormalized (using the percentile transformation) at each step of the aggregation
- Note: each of the 5 subcategories below will be tested separately as secondary analyses
- Diet + Exercise + BMI
  - Diet
    - *In a typical week, how often do you choose your food (the type and/or amount) with health and fitness concerns in mind? (more meals = better regulated)*
    - *In a typical week, how often do you eat more than you think you should eat? (more meals = less regulated)*
    - *Please indicate the degree to which the following statements describe your general tendencies: I tend to eat healthfully. (more like me = better regulated)*
  - Exercise
    - *How many of those hours [that you are active] represent exercise primarily intended to improve or maintain your health or fitness? (more hours = better regulated)*
    - *Please indicate the degree to which the following statements describe your general tendencies: I exercise often. (more like me = better regulated)*
  - BMI calculated as (weight in pounds / (height in inches \* height in inches) ) x 703
    - *How tall are you? Approximately how much do you currently weigh? (higher BMI = less regulated)*
    - Note: percentile and inverse normal calculations for BMI are done separately for men and women (i.e., z-scores are normally distributed for men and women separately)
- Smoking and Alcohol
  - Smoking behavior: each subject's smoking behavior is ranked such that non-smokers have the lowest rank and smokers are ranked by number of packs per week. (higher rank smoking behavior = less regulated)
    - *Do you smoke (including cigarettes, cigars, pipes, or anything else)? (smoker = less regulated)*
    - *If you smoke cigarettes, about how many packs do you smoke per week? (more packs per week = less regulated)*
    - One smoker did not indicate packs per week and is assumed to smoke the average number of packs per week of other non-smokers. Two smokers indicated 0 packs per week
  - Alcohol consumption for people who drink alcohol. This measure excludes people who reported 0 or missing for all three measures (days per week when drinking, drinks per day, and max drinks in last month) as they may be recovering alcoholics, not drink for religious reasons, etc.

- Number of drinks in a typical week calculated as days per week when drinking alcohol x typical number of drinks per day when drinking. (more drinks per week = less regulated)
    - *On average, how many days per week do you drink alcohol?*
    - *On a day when you drink, about how many alcohol drinks do you typically have?*
  - *In the past month, what is the maximum number of alcohol drinks you've had in one day (24 hours)? (more drinks = less regulated)*
- Preventative health and dental care
  - Preventative healthcare
    - *When your doctor gives you a prescription (excluding birth control), do you follow it exactly (for example, by taking all of the medication and taking it on the prescribed schedule)? (always adherent = more regulated)*
    - *How often do you visit your doctor for a routine check-up or preventive care? (more often = more regulated)*
  - Preventative dental care
    - *How often do you visit your dentist for a routine check-up or cleaning? (more often = more regulated)*
    - *How often do you floss your teeth? (more often = more regulated)*
- Agreement with statements about procrastination
  - *Please indicate the degree to which the following statements describe your general tendencies: (more like me = less regulated)*
    - *I needlessly delay finishing jobs, even though they are important.*
    - *I postpone starting in on things I don't like to do.*
    - *When I have a deadline, I wait until the last minute.*
    - *I delay making tough decisions.*
- Carefully consider future consequences of current financial decisions
  - *Please indicate the degree to which the following statements describe your general tendencies: I usually carefully consider the future consequences of my current financial decisions. (more like me = more regulated)*

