## T. Current emotional state and satisfaction with present relationship

- This is a secondary outcome as we consider it a noisy measure of emotional well-being and happiness in relationships that focuses on current emotional states and relationships rather than stable emotional and personality traits
  - The MOS SF-36 is designed to assess patient outcomes after a procedure or treatment and focuses on emotions in the last 4 weeks
  - Rather than being able to measure happiness across all past relationships, the satisfaction with present relationship measure is dependent on the individual's current relationship and their perception of "the average couple"
- After creating the aggregate variables for each subsection listed below, Z-scores are calculated by taking the inverse normal of the percentile ranks for each category. To create the composite measure, Z-scores are averaged across all five categories and renormalized at the end
- Role limitations due to emotional problems in the last 4 weeks: Scored based on the Medical Outcomes Study 36-item short-form (MOS SF-36) where "Yes" = 0 and "No" = 100. The three scores are averaged to a composite score and then transformed using the percentile-rank inverse normal distribution.
  - *During the past 4 weeks, have you had any of the following problems with your work or other regular daily activities as a result of any emotional issues (such as feeling depressed or anxious)?*
    - *Cut down the amount of time you spent on work or other activities*
    - *Accomplished less than you would like*
    - *Were limited in the kind of work or other activities*
    - *Had difficulty performing the work or other activities (for example, it took extra effort)*
    - *Didn't do work or other activities as carefully as usual*
- Health interfering with social activities in the last 4 weeks: Scored based on the MOS SF-36 as described below. The two scores are averaged to a composite score and then transformed using the percentile-rank inverse normal distribution.
  - *During the past 4 weeks, to what extent has your physical health or emotional problems interfered with your normal social activities with family, friends, neighbors, or groups? (Not at all = 100, Slightly=75, Moderately=50, Quite a bit=25, Extremely=0)*

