  - *During the past 4 weeks, how much of the time has your physical health or emotional problems interfered with your social activities with family, friends, neighbors, or groups? (All of the time=0, Most of the time=25, Some of the time=50, A little of the time=75, None of the time=100)*
- Emotions felt in the last 4 weeks: Scored based on the MOS SF-36 in increments of 20 points from 0 to 100 in the directions described below (e.g., more often = higher score). Scores are averaged to a composite score and then transformed with the inverse-normal transformation
  - *These questions are about how you feel and how things have been with you during the past 4 weeks. For each question, please give the answer that comes closest to the way you have been feeling. How much of the time during the past 4 weeks... (Responses: All of the time, Most of the time, A good bit of the time, Some of the time, A little of the time, None of the time)*
    - *Have you been a very nervous person? (more often = lower score)*
    - *Have you felt so down in the dumps that nothing could cheer you up? (more often = lower score)*
    - *Have you felt calm and peaceful? (more often = higher score)*
    - *Have you felt downhearted and blue? (more often = lower score)*
    - *Have you been a happy person? (more often = higher score)*

- Energy/fatigue in the last 4 weeks: Scored based on the MOS SF-36 in increments of 20 points from 0 to 100 in the direction described below (e.g., more often = higher score). The scores are averaged to a composite score and then transformed using the percentile-rank inverse normal distribution
  - *These questions are about how you feel and how things have been with you during the past 4 weeks. For each question, please give the answer that comes closest to the way you have been feeling. How much of the time during the past 4 weeks... (All of the time = lowest, None of the time = highest)*
    - *Did you feel full of pep? (more often = higher score)*
    - *Did you have a lot of energy? (more often = higher score)*
    - *Did you feel worn out? (more often = lower score)*
    - *Did you feel tired? (more often = lower score)*

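### Three scoring rules cannot be followed as written: one smoker is imputed from non-smokers, and two emotional-state subscales contradict their own item lists

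*SAP*

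**What the plan says.** **Smoking (SAP VIII.R).** Smoking is ranked so that "non-smokers have the lowest rank and smokers are ranked by number of packs per week". Smoking status comes from its own yes/no question. Quantity comes from a conditional one: "If you smoke cigarettes, about how many packs do you smoke per week". The missing-data note says that one smoker who gave no quantity "is assumed to smoke the average number of packs per week of other non-smokers", and then adds "Two smokers indicated 0 packs per week". The smoking score feeds the smoking-and-alcohol category, a secondary outcome (IV.A). That category is one of five in the index of forward-looking behaviors, a primary outcome with n = 113 (III.A).

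**Role limitations (SAP VIII.T).** Each item scores 0 for Yes and 100 for No. The rule is "The three scores are averaged to a composite score". Five items are listed beneath it.

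**Energy/fatigue (SAP VIII.T).** Items run from 0 to 100 in steps of 20, and the opening sentence defers to directions given further down. The question stem then carries a key for the whole block: "All of the time = lowest, None of the time = highest". Beneath it, "Did you feel full of pep" and the item on having a lot of energy are marked so that more often scores higher. The worn-out and tired items are marked the other way.

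**The concern.** The plan is meant to fix how each variable is built before any analysis is run (Section I). In these three places an analyst cannot follow the text without correcting it or guessing.

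- A known smoker is given a quantity from people who are not asked for one, in a component of a primary outcome.
- The role score does not say whether three or five items count or, if three, which.
- The energy block carries two scoring directions that cannot both hold for two of its four items.

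Two analysts working in good faith could produce different variables, and the choice could be made after results are known.

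**Working it through.** No sample-size or error-rate figure is involved. The check is a count, a rescoring under each reading, and a rank calculation.

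**1. Smoker.** From the SAP: N = 113, one smoker with missing quantity, two smokers at 0 packs, and smokers ranked above non-smokers. Assumed, because the SAP does not give them: S = 5 to 15 smokers in total, and the remaining S − 3 spread evenly over 1 to 7 packs per week. Score: z = Φ⁻¹((rank − 0.5)/N), where higher means more smoking and ties share the mean rank.

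Taken literally, the imputed value is 0 packs. The person stays a smoker and ties with the two other 0-pack smokers. For S = 5 the rank is 108 + 2 = 110, so z = Φ⁻¹(109.5/113) = 1.87. If other smokers are the reference group, the imputed mean is (0 + 0 + 1 + 7)/4 = 2 packs, the rank is 112, and z = Φ⁻¹(111.5/113) = 2.22.

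| Smokers assumed | z as written (0 packs, still a smoker) | z from other smokers' mean | Difference |
|---|---|---|---|
| 5 | 1.87 | 2.22 | 0.35 |
| 8 | 1.58 | 1.87 | 0.29 |
| 10 | 1.44 | 1.75 | 0.31 |
| 15 | 1.18 | 1.50 | 0.32 |

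The shift is about 0.3 to 0.4 z, and it makes this person look better regulated. Smoking is one of two parts of its category and the category is one of five, so its weight is 1/2 × 1/5 = 1/10. That gives about 0.03 to 0.04 SD on the index before renormalising.

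Effect on the primary coefficient: suppose this person's key independent variable is as extreme as x = 2. The coefficient then moves by about 0.04 × 2/113 = 0.0007. The standard error is near 1/√110 = 0.095 for standardised variables, so the move is under 1% of one standard error.

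**2. Role limitations.** Five items are listed against three stated.

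- Yes on items 4 and 5 only: the first three items give (100 + 100 + 100)/3 = 100; all five give (100 + 100 + 100 + 0 + 0)/5 = 60.
- Yes on items 1 and 2 only: the first three give (0 + 0 + 100)/3 = 33.3; all five give 60.

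Two respondents who tie on five items are therefore at 100 and 33.3 on the first three, so the rank order changes, and the percentile transformation works on ranks.

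**3. Energy/fatigue.** Order of items: pep, energy, worn out, tired.

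| State | Printed item directions | Block key on all four items |
|---|---|---|
| Best (all, all, none, none of the time) | (100 + 100 + 100 + 100)/4 = 100 | (0 + 0 + 100 + 100)/4 = 50 |
| Worst (none, none, all, all of the time) | (0 + 0 + 0 + 0)/4 = 0 | (100 + 100 + 0 + 0)/4 = 50 |

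Under the block key the two positive and two negative items cancel. Role limitations and energy/fatigue are two of the five categories averaged into the emotional-state outcome.

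**The case against.** The strongest reply is that these are drafting slips of little consequence, and most of it stands.

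- **The intent is mostly visible.** The word *other*, applied to someone the sentence calls a smoker, points to smokers as the intended group. In the energy block, each item carries its own direction and the opening sentence defers to those directions. The neighbouring emotions block has a plain response list where this key sits. Only the role-limitations count is left unsettled by the text.
- **A safeguard exists.** Section V repeats the relevant analyses without respondents whose data needed an assumption during cleaning, and this smoker is one of them. That covers the problem in part: it is a robustness check, and the main analysis keeps the rule as written.
- **The reach is narrow.** The role and energy slips touch one secondary outcome, which the authors themselves call noisy and which lies outside the false-discovery and joint Wald procedures of Section VI.

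A reader might infer something larger, namely that 0 packs ties the smoker with the non-smokers. With the same assumed counts that would be a shift of about 1.7 to 2.3 z (for S = 5, from 2.22 to −0.04; for S = 15, from 1.50 to −0.16), or roughly 0.2 SD on the index. The SAP does not support this. Status and quantity are separate questions, the ranking rule puts non-smokers lowest, and two people at 0 packs are still called smokers. A reader might also infer that the energy subscale will be cancelled in practice. That would require ignoring the printed directions of the pep and energy items, so it is a risk of the stray key and not the likely plan.

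What remains is that likely intent is not a written rule, and it does not show what the code does.

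**Conclusion.** All three rules need correcting, as minor points. The smoker rule is wrong as written but has a negligible effect on the primary coefficient. Its size rests on assumed smoker numbers and pack counts and on the 1/10 weight, which supposes that this person also has an alcohol score. The role-limitations rule cannot be carried out without guessing. The energy key contradicts two of its four items and should not be left for the programmer to resolve. Nothing here calls the primary conclusions into question.

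**What to change.** Before analysis:

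1. In VIII.R, replace *other non-smokers* with *other smokers* in the imputation note. No new ranking rule is needed, because the existing one already places 0-pack smokers above non-smokers. Confirm that the code ranks on status first and not on packs alone.
2. In VIII.T, role limitations: reconcile the stated count with the list and name the items that enter the score.
3. In VIII.T, energy/fatigue: delete the block key and score each item in the direction printed beside it.

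The cost is three wording edits and a code check. No new data are needed, and no hypothesis or model changes.
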